## Abstract

Due to population ageing and medical advances, people with advanced chronic diseases (ACD) live longer. Such patients are even more likely to face either temporary or permanent reduced functional reserve, which typically further increases their healthcare resource use and the burden of care on their caregiver(s). Accordingly, these patients and their caregiver(s) may benefit from integrated supportive care provided via digitally supported interventions. This approach may either maintain or improve their quality of life, increase their independence, and optimize the healthcare resource use from early stages. ADLIFE is an EU-funded project, aiming to improve the quality of life of older people with ACD by providing integrated personalized care via a digitally enabled toolbox. Indeed, the ADLIFE toolbox is a digital solution which provides patients, caregivers, and health professionals with digitally enabled, integrated, and personalized care, supporting clinical decisions, and encouraging independence and self-management. Here we present the protocol of the ADLIFE study, which is designed to provide robust scientific evidence on the assessment of the effectiveness, socio-economic, implementation, and technology acceptance aspects of the ADLIFE intervention compared to the current standard of care (SoC) when applied in real-life settings of seven different pilot sites across six countries. A quasi-experimental trial following a multicenter, non-randomized, non-concurrent, unblinded, and controlled design will be implemented. Patients in the intervention group will receive the ADLIFE intervention, while patients in the control group will receive SoC. The assessment of the ADLIFE intervention will be conducted using a mixed-methods approach.

## 1. Rationale

Due to population ageing and medical advances, people with chronic disease(s)—including advanced chronic disease(s) (ACDs)—live longer. Patients living with chronic disease may face either temporarily or permanently reduced functionalities, which typically increases their caregiver’s burden and their healthcare resource use [1,2].

Chronic Obstructive Pulmonary Disease (COPD) and Heart Failure (HF) are two of the most prevalent ACDs [3,4]. Both COPD and HF are important causes of morbidity and mortality [3,5] together with high social and economic costs [6,7]. Patients with such conditions may benefit from integrated supportive care provided via digitally supported interventions [8,9]. This approach may either maintain or improve their quality of life, increase their independence, and optimize the healthcare resource use from early stages [1,2]. However, there is limited evidence on the implementation of such approaches.

The EU-funded ADLIFE project (H2020, SC1-DTH-11-2019, 875209) aims to meet the current societal and health system challenges in Europe that are created due to the increasing number of persons living with ACD, often with accompanying co-morbidity and polypharmacy. ADLIFE is designed to provide to such patients and their caregiver(s) with digitally enabled, integrated, and personalized care. The ADLIFE toolbox is a digital solution which consists of three Information and Communication Technology (ICT) components: a platform to manage and customize care plans by the interdisciplinary healthcare team with the patient and for the patient, services supporting the clinical decisions, and a platform encouraging independence and self-management of patients and caregivers. The ICT solutions will be scaled in the seven pilot sites from six countries participating in the intervention in an integrated manner with the existing ICT solutions utilized for healthcare systems.

The ADLIFE intervention objective is to have an impact for three stakeholders: patients, informal caregivers, and healthcare professionals, across the seven participating international healthcare systems. Thus, the ADLIFE intervention aims at slowing down the patients’ functional deterioration ensuring their quality of life and promoting shared decision making, whilst in parallel reducing the caregiver burden, improving the healthcare professional’s working conditions, and optimizing healthcare resource use.

The evaluation of such an intervention is challenging, since multiple dimensions [10,11] arise. Published results have reported notable improvements in some of the primary outcome measures [12,13,14,15], but there is also lack of evidence-based changes in comparison with SoC [16,17,18,19,20]. Therefore, there is a lack of systematic assessments of the effect of personalized integrated care initiatives on patients with ACD and limited consistent evidence on the related impact on conventional and emergency department visits, hospital admissions, and length of hospitalization stay.

The aim of this research is to evaluate whether the ADLIFE intervention, when applied in real-life settings, is able to deliver appropriate targeted and timely care for patients living with ACD. Here we present the protocol of the ADLIFE study. Using a mixed-methods approach, this study will provide robust scientific evidence on the effectiveness, socio-economic implementation, and technology acceptance assessment of ADLIFE compared to the SoC, in order to provide the scientific evidence-based supporting the funding decision-making of the ADLIFE intervention.

## 2. Methods and Analysis

### 2.1. Study Design

The ADLIFE intervention is a quasi-experimental trial following a multicenter, A quasi-experimental, non-randomized, non-concurrent, unblinded, and controlled design. Patients belonging to the intervention group will receive the ADLIFE intervention, while patients in the control group will receive SoC [21]. The SoC description can be found in Supplementary File S1. The trial will be implemented in a real-life setting thus allowing other programs and behavior interventions can be in place. The ADLIFE intervention will be implemented in seven different pilot sites: Basque Country (Osakidetza), United Kingdom (National Health Service Lanarkshire and University Hospitals Coventry and Warwickshire National Health Service Trust), Denmark (Odense University Hospital), Germany (Gesunder Werra-Meißner Kreis), Sweden (Region Jämtland Härjedalen), and Israel (Assuta Ashdod Hospital—Maccabi Healthcare Services Southern Region) involving healthcare professionals, care services, and patients with their caregiver(s). The trial was registered in ClinicalTrials.gov, accessed on October 2022. Number of identification: NCT05575336. The study will be conducted in line with the ethical standards and the applicable European, international, and national law on ethical principles. Ethics approval will be obtained from all pilot sites’ Ethics Committee. Patients and caregivers will provide written informed consent.

#### 2.1.1. Non-Randomized, Non-Concurrent, and Unblinded

The non-randomized design of the ADLIFE clinical trial lies on the recruitment process, as detailed in Section 2.3. To address potential biases and guarantee comparability between the control and the intervention group caused by the afore-mentioned non-random design, the control group selection will be based on a propensity score matching with the intervention group [22]. First, the probability of all eligible individuals of being assigned to the intervention group will be estimated using the patient variables of age and sex, and the number of emergency room (ER) visits and number of hospital admissions observed during the 9 months prior to the ADLIFE intervention. Then, each intervention patient will be matched to a control subject with a similar propensity of being assigned to intervention.

The control group will be retrospectively selected to guarantee that the control group receives usual care. The study will be unblinded, since all stakeholders involved in the intervention group will use the ADLIFE toolbox and will thus be aware of the intervention However, since data will be retrospectively collected from the electronic health records (EHR) for the control and the intervention group, no information bias is expected in the data collection process. The study design and the data collection flow are shown in Figure 1. Data collection is also described in Section 2.7 of this paper.

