### 2.2. Study Population

The study population consists of patients with ACD, their informal caregiver(s), and their healthcare professionals, meeting the following eligibility criteria. Eligible patients will have to meet the below inclusion criteria:Aged over 55;HF in functional stage III/IV according to the NYHA scale and/or stages C and D of the ACCF/AHA classification. Stable phase (at least two months without decompensation requiring hospital care);And/or COPD GOLD scale > 2 (FEV1 < 50) and/or mMRC ≥ 2 and/or CAT ≥ 10 and/or use of oxygen at home;With or without comorbidities;They are able to provide informed consent;They still live and generally plan on living in their home for the intervention duration;They or their informal caregiver(s) are able to use digital technology, communication tools, and/or networks and have access to a computer, laptop, tablet or smartphone and wifi/internet connection;They or their informal caregiver(s) understand, read, and talk the native language.

The informal caregiver will be a person who provides occasional or regular support to the patient needs. Caregivers will be eligible if the patient they care for meets the inclusion criteria and is included in the study. Healthcare professionals will be eligible if they are involved in the included patients’ care, are open to new ways of working, specifically as part of a coordinated and collaborative team, and are also open to the use of new technology. Criteria for patient exclusion include an existing diagnosis of an active malignant neoplastic disease, being in any active list of transplantation, or refusing/unable to sign the informed consent. Patients who have withdrawn their participation from ADLIFE will be excluded; caregivers will not be eligible if the patients they care for meet the exclusion criteria; Healthcare professionals not caring for eligible patients will not be included.

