### 2.3. Recruitment

The recruitment of healthcare professional, patients and caregivers will last 7 months. Healthcare professionals will be recruited during the first 4 months by each pilot site using a convenience sampling based on their individual profiles. The healthcare professionals will be contacted via email, letter, or face-to-face meeting to provide them with initial information about the ADLIFE intervention. Healthcare professionals consenting to participate will be recruited.

Once healthcare professionals have been recruited and trained in the use of the ADLIFE intervention, each pilot site will identify a tentative target patient population fulfilling the eligibility criteria from EHR. After a validation process conducted by the healthcare professionals, a final target population will be defined.

The intervention and control group will be recruited from the final target population during the last 2 months. Candidates for the intervention group will be recruited by healthcare professionals or research assistants according to the inclusion/exclusion criteria. They will be contacted by email, post, phone, or face-to-face meetings, and provided with information describing the ADLIFE intervention, their expected role, and their required ICT skills. Patients participating in the intervention will sign an informed consent and will receive ADLIFE intervention training.

Patients in the intervention group may appoint an informal caregiver who will participate with them in ADLIFE in order to assist them with ICT management and self-management empowerment of their disease. Informal caregivers will sign an informed consent to participate in the intervention, and a second informed consent to access their corresponding patient’s data. They will receive ADLIFE training together with the corresponding recruited patient they care for.

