## 3. Discussion

This study will conduct a holistic evaluation, not only based on a mixed-methods approach addressing the effectiveness, technology acceptance, and socio-economic impact, but also by involving the key stakeholders: patients, caregivers, and healthcare professionals. In addition, the use of the health outcome framework will shape the scientific evidence compared to the SoC. Study findings will be disseminated through peer-reviewed publication and scientific conferences [48].

However, this study is not free of limitations. The first is related to the recruitment process. The healthcare professionals/research assistants will recruit the intervention participants according to their subjective assessment, which will not allow for the participants’ randomization. Second, the design of the data collection process, where the control period information will be retrospectively collected, will not allow the quality of life to be used as a main outcome. Moreover, thirdly, the existing differences in the ADLIFE intervention and the SoC across the different health systems might lead to a bias of the ADLIFE global effect. To address this twofold concern, the ADLIFE intervention must first be defined as a pragmatic trial [49] of a complex intervention [50]. Pragmatic trials measure effectiveness in routine clinical practice and its design reflects variations across patients. While interventions should be precisely described in Randomized Control Trials (RCT), in pragmatic trials this does not imply that the same interventions are offered to each patient. Indeed, clinicians and patients’ biases are not necessarily considered as a weakness but accepted as part of the physicians and patients’ responses to the intervention, and therefore included in the overall assessment [51]. Pragmatic trials may vary across similar participants, by chance, by practitioner preference, and according to institutional policies.

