**Figure 2 ijerph-20-03152-f002:**
[figure not shown]
Flow-chart of the recruitment and selection process. * TCPP is defined as the subset of final target population after removing the intervention patients.

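### Matching on age, sex and prior use alone cannot guarantee comparability: site, index disease and severity are left out, and the status of patients who refuse consent is unresolved

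*Protocol article*

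**What the plan says.** Section 2.1.1 gives the purpose of the matching as "To address potential biases and guarantee comparability between the control and the intervention group". The probability of being in the intervention group is "estimated using the patient variables of age and sex, and the number of emergency room (ER) visits and number of hospital admissions" during the 9 months before the intervention, after which "each intervention patient will be matched to a control subject with a similar propensity of being assigned to intervention".

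On how the groups arise, section 2.3 states: "The intervention and control group will be recruited from the final target population during the last 2 months". Each site identifies that population from its EHR, and professionals validate it. Intervention candidates are then approached, told what ICT skills are needed, and sign consent. The Discussion adds: "The healthcare professionals/research assistants will recruit the intervention participants according to their subjective assessment".

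Section 2.3 forms the control pool by taking the intervention patients out of the final target population. The Figure 2 legend agrees: "TCPP is defined as the subset of final target population after removing the intervention patients". Controls need no consent, and the only people expressly barred from the pool are intervention patients who withdraw. Section 2.2 lists among the patient exclusions "refusing/unable to sign the informed consent".

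Section 2.9.1 includes site as a random effect and adjusts all models for potential confounders, which it does not name.

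**The concern.** Without randomisation, the primary comparison of ER visits rests on how controls are chosen and what is adjusted for. The matching variables are the part of that safeguard the article states in detail, and it presents them as sufficient.

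Staff judging who suits a digital self-management programme may well respond to disease, severity, general condition and willingness. Each of these can also affect ER use, and none is in the score. A patient with end-stage HF at one site could be matched to a patient with COPD at another if age, sex and prior use give a similar score.

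Consent is a second filter. Every intervention patient has agreed to take part, whereas the control pool, read literally, can include people who were asked and declined.

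Confounding of this kind does not shrink with sample size. The estimate is also meant to inform funding decisions (Rationale) and feeds the budget impact model (section 2.9.3).

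**Working it through.** **1. What the matching covers**

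| Factor | Where the article uses it | In the matching? | Other control |
|---|---|---|---|
| Age, sex | 2.1.1 | Yes | – |
| ER visits and admissions, prior 9 months | 2.1.1 | Yes | – |
| Pilot site | 2.1, 2.9.1 | Not stated | Random effect |
| HF, COPD or both | Entry criterion, 2.2 | No | Possibly an unnamed covariate |
| NYHA or ACCF/AHA stage, GOLD, mMRC, CAT, home oxygen | Entry criteria, 2.2 | No | Range limited by entry; possibly an unnamed covariate |
| Comorbidity | Allowed, 2.2 | No | Possibly an unnamed covariate |
| Willingness to take part | Consent, 2.2 and 2.3 | No | None stated |

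Because sites screen the entry criteria from the EHR (2.3), at least some disease and severity fields should be available for controls.

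**2. Patients who refuse**

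The target population is fixed before anyone is approached, so refusal becomes known only later. Target population minus intervention patients then leaves never-approached patients and those who declined. Section 2.2 excludes the latter. The two rules agree only if a step not described in the text removes decliners, or if the consent criterion was never meant to apply to controls.

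**3. Illustrative size**

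The article gives no figure for imbalance or bias, so there is none to reproduce. The only figure taken from it is the target effect: 0.6 visits per year (2.6), or 0.6 × 9/12 = 0.45 per 9 months. All other inputs here are assumptions.

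*Additive scale.* Spurious difference = residual imbalance × difference in ER visits attached to the factor.
- 0.10 × 0.6 = 0.06 per year; 0.06/0.6 = 10% of target.
- 0.20 × 1.2 = 0.24 per year; 0.24/0.6 = 40% of target.

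*Ratio scale.* With no true effect and a marker that doubles the ER rate, the apparent rate ratio is (1 + p_int)/(1 + p_ctl), where p is the marker's residual prevalence in each group.
- 15% v 30%: 1.15/1.30 = 0.885.
- 20% v 30%: 1.20/1.30 = 0.923.
- With an assumed control rate of 0.9 to 1.5 visits per 9 months: 0.9 × (1 − 0.923) = 0.07 and 1.5 × (1 − 0.885) = 0.17, or 15% to 38% of 0.45.
- Reversing the first imbalance gives 1.30/1.15 = 1.13, against the intervention.

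*How much the four variables help.* In a simulation with no treatment effect, patients were matched 1:1 to the nearest propensity score on the four listed variables, with no outcome-model adjustment. Less severe patients were assumed likelier to be recruited, and in the last two settings more willing patients also had lower ER use. The bias in visits per year, before and after matching, was:

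| Before | After | Removed |
|---|---|---|
| −0.054 | −0.050 | 7% |
| −0.099 | −0.057 | 42% |
| −0.156 | −0.124 | 21% |
| −0.106 | −0.079 | 25% |
| −0.294 | −0.193 | 34% |

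The negative sign follows from the assumed selection. The useful result is that matching on prior use reduced the bias without removing it.

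**4. What balance can be asked for**

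The chance standard deviation of a standardised difference is about √(2/n per arm).
- Within a site, assuming equal sites: 846/7 ≈ 121 per arm, so √(2/121) = 0.13. Under randomisation, P(|difference| > 0.1) ≈ 44%.
- Overall: √(2/846) = 0.049, so the same probability is about 4%.

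**The case against.** The strongest defence is that the article relies on more than the four variables. Both groups come from one professionally validated population restricted to advanced HF and/or COPD. Prior ER use is the baseline version of the outcome and a partial proxy for severity. Site is a random effect, and the Discussion names it as the control for differences between health systems. Models adjust for confounders whose list may properly sit in an analysis plan not shown. The Discussion openly concedes subjective recruitment. All of this stands, and it makes large residual confounding less likely. It does not make the promise of comparability true, and a site intercept neither balances severity within a site nor deals with willingness.

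Several stronger readings are tempting but unsupported:

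- *Site is ignored.* Sites identify their own populations and extract their own control data. Within-site matching is unstated, not ruled out.
- *The plan certainly contradicts itself on refusers.* Section 2.1.1 fits the score to all eligible individuals. If the refusal criterion binds controls, decliners are already out; if consent governs participation only, there is no conflict. The Figure 2 flow-chart is not shown and may include a removal step. What stands is that the text, on its face, leaves decliners in.
- *The bias favours the intervention.* Nothing in the document shows that decliners are frailer, and staff could equally favour patients with greater need.

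**Conclusion.** The concern holds as a weakness in a stated design choice. Four variables cannot guarantee comparability when recruitment is subjective and depends on consent, and a better variable set is within reach because sites already screen on disease and severity. The other safeguards reduce residual confounding but do not ensure that it is gone.

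Its size and direction cannot be derived from the document. A reader might take the 10% to 40% of the target effect as an estimate of bias in this trial. It is not: it assumes the imbalance left after matching and adjustment, and the sign could go either way. It shows only that moderate residual imbalance would matter against a target of 0.6 visits per year.

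On refusal, the conclusion is that sections 2.2 and 2.3 and the Figure 2 legend need reconciling, not that an eligibility breach is established.

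**What to change.** Before controls are selected:

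1. State that matching is done within pilot site.
2. Add index disease (HF, COPD, both) and the severity markers already screened (NYHA or ACCF/AHA stage, GOLD, home oxygen, where recorded) to the propensity score, with comorbidity where available. Name the same variables as covariates in the outcome model. Exact matching on site and disease together is not needed: 7 × 3 = 21 strata would average about 846/21 ≈ 40 intervention patients each.
3. Reconcile sections 2.2 and 2.3 and the Figure 2 legend on patients who refuse. Run the primary analysis with and without them as a sensitivity analysis. Removing known refusers alone would still leave would-be refusers among patients never approached.
4. Replace the guarantee of comparability with reported standardised differences, judged overall. A 0.1 limit in each site would be missed too often by chance.

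The cost is protocol and analysis-plan wording, some additional EHR fields, and a record of who was invited and declined. The downsides are some missing staging data (entry criteria are joined by and/or, so a patient may qualify on mMRC or CAT without a recorded GOLD stage), a somewhat smaller control pool and a few unmatched patients.
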